Can participation in the team sports and individual sports conditions be explained by the constructs of the Sport Commitment Model?We hypothesize that participation will be predicted by sports commitment as per the tenets of the Sport Commitment Model. Commitment will be predicted primarily by enjoyment (+), social constraints from family obligations/involvement alternatives (−), and social involvement opportunities/personal investments (+).Can group differences among these motivational and behavioral outcomes be explained through a mediation model?We propose that the covariance of the assigned conditions on psychosocial outcomes will be explained by sport participation. In turn, the covariance between participation and assigned conditions will be explained by salient underlying motives from the Sport Commitment Model. In particular, enjoyment will explain the differences between both sport conditions, but the better psychosocial outcomes from team sports will be explained by the additional involvement opportunities of friendship and social interaction.Is there a seasonal, gender, dual/single parent, age of child, or type of sport difference across primary outcomes by assigned condition?Differences in season, gender, age of child, and type of sport are exploratory research questions. It is possible that both sport conditions may have participation lowered by weather conditions in the winter. Men may participate in sport more due to lower childrearing expectations; however, there is currently limited research to support this conjecture. Similarly, younger children may impact sport participation because of the considerable care needs of young children. Finally, it is possible types of sport could differ in their psychosocial outcomes for reasons such as the structure or environment of participation.

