### Participants and eligibility

Parents are considered eligible if they reside in Victoria, British Columbia, and have at least one child under 13 years of age who resides in the home. This cutoff was delimited as such because it represents the lower bound of the teenage years, when children still have substantial care needs. It follows parents with children under 13 have numerous familial obligations and subsequently experience notable time constraints. Both mothers and fathers are eligible, inclusive of those with single status. Parents must not engage in regular sport participation (operationally defined as not having participated in an organized sport in the month prior to baseline). Parents must also be below the recommended physical activity guidelines (150 min of weekly moderate to vigorous physical activity [19]), which is determined via self-report at the initial screening interview. Parents need to be willing to participate in a team sport in addition to being deemed safe to engage in moderate-intensity physical activity (assessed via the Get Active Questionnaire [31];). Those individuals who are not ready or able to participate in moderate-intensity physical activity will be excluded for safety reasons. Mental health conditions such as depression and anxiety do not preclude participation, because these are not contraindications to beginning a physical activity program [32].

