##### Sport commitment and sport participation

Parents are also assessed on the constructs of the Sport Commitment Model [20] at three time points: baseline, 6 weeks, and 3 months. The Sport Commitment Model [20] is measured by the associated sport commitment questionnaire with the adjusted measures for adult samples relevant to parents of children [26, 42]. Previous sport commitment research among adult fitness participants has shown the questionnaire to have acceptable validity and reliability in the measurement of sport commitment, enjoyment, involvement alternatives, personal investments, social constraints, and involvement opportunities [24]. The questionnaire wording was slightly modified in order to be framed for both sport and physical activity.

Additionally, at the final 3-month measurement, condition adherence/sport participation is assessed with a study-created item, “How was your attendance for your condition (team sport, individual sport, or personal time)?” with possible answers of “did not adhere at all,” “missed over half the sessions (at least 6),” “missed 3–4,” “missed 1–2,” and “did not miss any sessions.” An additional item assesses reasons for missing sessions with responses including common barriers for parents, such as “too tired,” “couldn’t get childcare,” “work commitments,” and “family commitments.” Last, four items rated on a scale from 1 (strongly disagree) to 5 (strongly agree) asks participants the extent to which their condition was enjoyable, beneficial, or challenging and how much they looked forward to their weekly activity. Condition adherence/sport participation is also complemented by a phone-assisted report of attendance at the 6-week assessment and an in-person report at the final 3-month interview.

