### Analysis strategy

Missing data will be inspected to determine the appropriate imputation procedures [43], and normality of all variables will be checked to determine whether any transformations are required. To determine whether psychosocial outcomes change over time similarly for all three conditions (i.e., to address objective 1), a level 1 model will be specified wherein the intercept (i.e., value of the outcome at baseline) will be allowed to vary randomly (i.e., vary across participants) and the slope for the linear trend will be constrained to be fixed (i.e., the same across participants), controlling for any significant covariates at level 2. Additionally, dummy variables will be created for condition (team sports: 1 = yes or 2 = no; individual sport: 1 = yes or 2 = no; control: 1 = yes or 2 = no) at level 2, with the team sport and individual sport variables being added to the model to predict the intercept and slope at level 1. In doing so, the control group is compared with the other two groups to determine if baseline psychosocial outcomes are similar across conditions and whether the change is similar across conditions. Follow-up analyses will be conducted for the group comparison. To determine whether participation within the team and individual sport conditions is explained by the Sport Commitment Model constructs (i.e., secondary objective 1), a time-varying covariate analysis will be used. For example, within the team sport condition, participation will be predicted by a level 1 model that includes a random intercept, fixed slope, and the time-varying Sport Commitment Model constructs. The same will then be done for the individual sport condition. To determine whether the change in the underlying motives explains the potential change in sport participation during the intervention similarly for all three groups (i.e., to address secondary objective 2), a time-varying covariate mediation analysis approach will be used following the procedure outlined by Krull and MacKinnon [44] for level 1 mediation. Briefly, the analyses needed to establish mediation will treat the underlying motives as time-varying covariates at level 1 of the model. Then, the dummy-coded condition variables will be entered at level 2 to determine if the mediation relationships are similar across groups. Finally, to determine whether there is a seasonal, gender, or sport type (within team or individual) difference across the primary and secondary outcomes (i.e., to address secondary objective 3), each variable will be entered into the various models at level 2 to predict the intercepts and slopes at level 1. Doing so will determine if they impact the change in the various outcomes across time.

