
### Justification of sample size

Given the hierarchical nature of the data (i.e., the three measurement occasions at level 1 were considered to be nested within the participant at level 2), the optimal design program for power estimation of hierarchical linear models [45] was used. With three measurement occasions, three groups, and a small to moderate effect size (0.40), a total of 207 participants (i.e., 67 parents per condition) were needed to show significant differences over time. Inclusive of a potential 25% attrition rate, the total sample size required is 240.

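### Secondary question 1 asks whether commitment predicts participation, but the planned unlagged model pairs attendance already reported with motives measured afterwards, so it cannot show direction

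*Protocol article*

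**What the plan says.** Under Present research aims and hypotheses, the first secondary question carries a directional hypothesis: "We hypothesize that participation will be predicted by sports commitment as per the tenets of the Sport Commitment Model".

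The Analysis strategy answers it within each sport arm. It says "a time-varying covariate analysis will be used", and for the team sport arm that "participation will be predicted by a level 1 model that includes a random intercept, fixed slope, and the time-varying Sport Commitment Model constructs"; the individual sport arm is handled the same way. No lag between constructs and participation is given.

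On timing, the section Sport commitment and sport participation places the constructs at baseline, 6 weeks and 3 months. It places the attendance item at 3 months, complemented by a "phone-assisted report of attendance at the 6-week assessment and an in-person report at the final 3-month interview". The Intervention description adds that the 6-week telephone report covers the preceding six weeks, and that parents in the sport arms are asked to track their own attendance.

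The answer options of the 3-month item go from one or two missed, to three or four missed, to an option that begins "missed over half the sessions (at least 6".

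**The concern.** The Sport Commitment Model is used here as an account of why people keep taking part. A test of it needs commitment recorded before the participation it is meant to explain. As written, the 6-week constructs are paired with attendance in the weeks before them, and the 3-month constructs with attendance before those. A parent who attended often and came to like the sport gives the same data pattern as a parent whose commitment led to attendance. The trial could report support for the model when the relation runs only the other way.

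The attendance item feeds the same analysis. A parent who missed exactly five sessions has no correct answer and must choose a neighbouring category.

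**Working it through.** The documents give no power or sample size figure for this question, so there is no stated figure to reproduce. The check sets the timings side by side and then illustrates the consequence.

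**Timing of each pair in a same-visit model**

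| Visit | Attendance refers to | Constructs measured | Order |
|---|---|---|---|
| Baseline | none; the sport is not yet assigned | before randomization | no assigned-sport attendance exists |
| 6 weeks | the preceding six weeks | at 6 weeks | predictor after outcome |
| 3 months | sessions already held | at 3 months | predictor after outcome |

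Both informative rows have the predictor recorded after the outcome. Adding the baseline row tells us nothing about attendance at the assigned sport. Removing it leaves two rows with the same problem.

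**Illustration A: two directions compared.** The arm size of 67 comes from Justification of sample size; everything else is assumed. There were 200 runs of a mixed model with a random intercept and fixed slope, and baseline attendance was constant. Write p1 and p2 for attendance in the two intervals, m0, m1 and m2 for the motive at the three visits, and e for independent standard normal noise.

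- Reverse only: p1 = e; p2 = 0.5·p1 + 0.87·e; m1 = 0.6·m0 + 0.5·p1 + 0.6·e; m2 = 0.6·m1 + 0.5·p2 + 0.6·e.
- Forward only: p1 = 0.5·m0 + 0.87·e; m1 = 0.6·m0 + 0.8·e; p2 = 0.5·m1 + 0.87·e; m2 = 0.6·m1 + 0.8·e.
- Null: no link either way.

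| Truth | Same-visit, three occasions: mean coefficient; rejected at 5% | Motive at interval start: mean coefficient; rejected at 5% |
|---|---|---|
| Reverse only | 0.37; 100% | 0.00; 5.5% |
| Forward only (0.50) | 0.21; 73% | 0.51; 100% |
| Null | 0.00; 5% | −0.01; 4.5% |

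The same-visit model gave a larger coefficient when the hypothesis was false (0.37) than when it was true (0.21).

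**Illustration B: does the number of occasions matter?** This used 67 per arm, 1000 runs, least squares with clustered errors and no true effect of commitment on attendance.

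| Assumed reverse effect | 0.2 | 0.3 | 0.5 |
|---|---|---|---|
| Same-visit, three occasions | 31% | 53% | 90% |
| Same-visit, 6 weeks and 3 months only | 62% | 92% | 100% |
| Motive at interval start | about 6–7% in all three settings | | |

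Dropping baseline does not help; here it makes the false-positive rate higher.

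**Limit of simple lagging.** If attendance persists within a person (correlation 0.5 between intervals), a lagged model fitted by least squares with clustered errors rejects in about 14% of runs at a reverse effect of 0.3 and about 25% at 0.5. With a random intercept it stays at about 6–7%, and adjusting for earlier attendance also brings it to about 6–7%. The fix below includes both.

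**The case against.** The strongest reply is that a journal article condenses the plan and may leave a lag to the full document. That has some force: if the full plan specifies a lag, only the wording here needs changing. But the article does name the model and its level 1 terms, and an unqualified time-varying covariate ordinarily means a same-occasion one.

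The research question itself is worded in terms of explanation, which an association might loosely satisfy. The hypothesis under it, however, speaks of prediction.

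The sizes above are driven by assumed paths, and the documents give no reverse effect. That objection stands, so the figures are illustrative only.

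The lagged test is also imperfect. Baseline commitment is measured before the sport is assigned and chosen, among parents not doing sport, so the first lag is a weak test of a theory about continuing.

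Three stronger readings are tempting and not supported:

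- *Participation is modelled at three occasions, is zero for everyone at baseline, and so the random intercept has no variance.* Eligibility is "operationally defined as not having participated in an organized sport in the month prior to baseline", which fixes organized sport only; some activity below the guideline is allowed, and the baseline questionnaire includes sport behaviour items that are not described. The statement that "the three measurement occasions at level 1 were considered to be nested within the participant at level 2" comes from the sample size section, and "the intercept (i.e., value of the outcome at baseline) will be allowed to vary randomly" is written for the primary objective. Nor does a constant baseline by itself remove intercept variance: with a fixed slope, the random intercept is a shift shared by all of a person's occasions. With categorical time and correlations of 0.3, 0.5 and 0.7 between the two attendance reports, a simulation gave intercept variances of about 0.10, 0.17 and 0.23. In Illustration A, with straight-line time, the variance was near zero, so the result depends on the setting.
- *Six missed sessions cannot be more than half.* The number of scheduled sessions is not stated. Six is over half of 10 or 11 sessions but not of 12 or more. Only the gap at five is certain.
- *The trial's main result is compromised.* This analysis serves a secondary question only.

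**Conclusion.** The concern holds in this form: as stated, the analysis of secondary question 1 can show that commitment and attendance go together, but not that commitment predicts attendance. This follows from the timing of the measurements and holds for two or three occasions. It rests on reading the time-varying constructs as same-visit values, which is the ordinary meaning where no lag is given.

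The size cannot be fixed from the documents. Under assumed reverse effects of 0.2 to 0.5, the false-positive rates shown run from 31% to 100%, against about 5–7% for a lagged model when attendance does not persist or the person-level random effect is kept. The missing option for five missed sessions is a separate, plain error in the item. Both are inexpensive improvements to a secondary objective.

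**What to change.** In the Analysis strategy, for secondary question 1:

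1. Model participation over two follow-up intervals only: weeks 0–6, and week 7 to 3 months.
2. Use the constructs from the start of each interval as predictors: baseline constructs for the first, 6-week constructs for the second.
3. Include a term for interval, keep the person-level random effect, and adjust for first-interval attendance in the second interval.
4. Score both intervals as sessions attended out of sessions scheduled, from the 6-week telephone report, the 3-month in-person report and the participants' own tracking. The 3-month item asks about the whole condition, so it cannot isolate the second interval alone.
5. If the same-visit model is kept, report it as an association.

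For the 3-month item, record the number of sessions missed for the remaining participants. These counts can be collapsed to the old categories for comparison with the 109 parents who have already completed the 3-month measures. A rule for a count of five should be stated in advance, since the old item offers no place for it.

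The cost is revised analysis wording and one reworded item, with no new visits. The downsides are two intervals instead of up to three occasions, 3-month constructs no longer used as predictors, a first lag that relies on commitment measured before the sport is chosen, and two item formats across waves.

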The model has sound validation in various sport domains, including amateur youth sport, elite-level sport, health club fitness participation, and competitive sport among adolescents [20, 23–25]. Studies show that all five of the proposed antecedents of the model can predict commitment and that commitment reliably predicts sport participation. However, there is a paucity of research applying the model in a recreational sport setting among adults. To this end, only one study has applied the model to understand adult recreational sport [26]. This study sought to validate the sport commitment model in an adult recreational setting, namely tennis. Acceptable indices of fit indicated that the model has utility in understanding adult recreational sport participation. Furthermore, the model seems particularly applicable to parents because relevant antecedents of participatory behavior such as alternatives (child care and support, domestic activities), involvement opportunities (friendship and social interaction), and social expectations may play key roles in defining who continues to participate in sports. Finally, the model may assist in identifying potential mechanisms for the psychosocial outcomes. The present study aims to examine the conjecture that enjoyment and opportunities for social involvement act as key mediators for team sport participation over individual sport involvement [27, 28]. In sum, the present study seeks to fill a gap in the contemporary literature by examining the effects of both individual and team sport compared with a control condition, as well as the social and enjoyment mechanisms proposed as mediators of this relationship through application of the Sport Commitment Model [20].

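### The mediation analysis for secondary question 2 contains no psychosocial outcome, so it addresses only part of what that question hypothesises

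*Protocol article*

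**What the plan says.** Under Present research aims and hypotheses, secondary question 2 reads "Can group differences among these motivational and behavioral outcomes be explained through a mediation model". The hypothesis beneath it has several parts:

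- On participation as a mediator: "We propose that the covariance of the assigned conditions on psychosocial outcomes will be explained by sport participation".
- On motives as a mediator of participation: "the covariance between participation and assigned conditions will be explained by salient underlying motives from the Sport Commitment Model".
- On social opportunity: "the better psychosocial outcomes from team sports will be explained by the additional involvement opportunities of friendship and social interaction". The same sentence says that enjoyment accounts for differences between the two sport conditions, without naming the outcome in which they differ.

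The Theoretical framework section presents the study as examining the effects of both sport types against control, "as well as the social and enjoyment mechanisms proposed as mediators of this relationship".

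The Analysis strategy section links one analysis expressly to secondary objective 2. It is a level 1 (within-person) mediation following a cited procedure. Its stated purpose is: "To determine whether the change in the underlying motives explains the potential change in sport participation during the intervention similarly for all three groups". The motives are time-varying predictors at level 1. The condition dummies are then "entered at level 2 to determine if the mediation relationships are similar across groups".

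**The concern.** The hypothesis starts at randomized condition and, in two of its parts, ends at psychosocial outcomes. The analysis assigned to it ends at sport participation. A variable that the hypothesis treats as a mediator has become the dependent variable, and the outcome to be explained is absent.

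At stake is what the trial may say about mechanism. Finding that motives track participation to a similar degree in all arms does not show why team sport improves quality of life, or whether attending sessions carries the benefit. If that result were reported as mediation of the psychosocial effect, the conclusion would not follow from the model fitted.

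**Working it through.** The documents give no figure to reproduce, so the check compares the hypothesised links with the variables and roles in each planned model.

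**Links hypothesised for question 2**
1. Condition → participation → psychosocial outcome.
2. Condition → motives → participation (the middle link).
3. Team versus individual sport → social involvement opportunities → psychosocial outcome. Enjoyment joins this link if the hypothesis is read together with the Theoretical framework section.

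**Analysis stated for secondary objective 2**
- Dependent variable: sport participation.
- Explanatory variables: the motives, within person.
- Stated purpose of entering condition: to compare the relation across arms.
- Psychosocial outcome: none.

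**Comparison**
- Link 1 needs participation as mediator and a psychosocial outcome as dependent variable. Neither is present, so the link is not tested.
- Link 2 needs the effect of condition on motives, and of motives on participation given condition. The second relation is in the plan. The text does not state that the first is estimated or that an indirect effect of condition is formed, so the link is partly addressed.
- Link 3 needs a psychosocial outcome as dependent variable. None is present, so the link is not tested.

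**Whether another planned model fills the gap**
- The objective 1 model has psychosocial outcomes and condition, but no mediator.
- The secondary objective 1 model predicts participation from the Sport Commitment constructs separately within each sport arm, so it contains no contrast between arms.
- The secondary objective 3 models add season, gender and sport type as predictors of intercepts and slopes, with no mediator.

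None of them does.

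**Illustration.** A model that omits the psychosocial outcome must give the same estimates however that outcome is generated. A simulation with assumed coefficients (20,000 per arm, three occasions, ordinary least squares point estimates) shows this; it illustrates the logic and is not evidence about this trial. Two scenarios shared the same condition, motive and participation data.
- Planned form, participation regressed on time and motive with condition interactions: motive slope 0.504, and motive-by-condition terms of −0.004 for each sport arm, in both scenarios.
- Psychosocial outcome as dependent variable, team-versus-control slope. Where participation carries the effect: total 0.163, direct 0.010, indirect 0.152. Where it carries none: total 0.159, direct 0.160, indirect −0.001.

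The planned form cannot separate the two scenarios; a model containing the psychosocial outcome can.

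**Data available for a repair.** Under Outcome measures, the psychosocial outcomes and the Sport Commitment constructs are measured at baseline, 6 weeks and 3 months. Attendance is reported only at 6 weeks and 3 months. The intervention section asks only the two sport arms to keep track of attendance, although the 3-month attendance item is worded for all three conditions.

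**The case against.** The best defence has four parts.

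*The question is about motives and behaviour.* Its opening line names motivational and behavioural outcomes, and the middle link is motives to participation, which the planned model does concern. This stands in part. A reader might infer that secondary question 2 goes wholly unanswered; the documents do not support that. But the hypothesis under the same question names psychosocial outcomes twice, and those parts have no analysis.

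*The article is condensed.* It describes the mediation steps in brief and relies on a cited procedure that is not at hand. In the objective 1 model, entering condition at level 2 means predicting both intercept and slope, so it need not mean moderation alone. A reader might infer that condition is certainly just a moderator and that no effect of condition on motives would ever be estimated. The stated purpose favours the moderator reading, but the text does not settle it. What can be said is that no decomposition of the condition effect is stated. The missing psychosocial outcome is a different matter: the article states both the purpose and the dependent variable, and a cited procedure does not supply another outcome.

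*The enjoyment chain is ambiguous.* A reader might infer that the hypothesis explicitly runs from enjoyment to psychosocial outcomes. It says only that enjoyment accounts for differences between the sport conditions. The Theoretical framework section makes the psychosocial reading plausible, but only social involvement opportunities are tied to psychosocial outcomes in so many words.

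*The question is secondary.* That is true, and it limits the importance of the point.

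**Conclusion.** The point holds as a mismatch between a secondary hypothesis and its analysis. The planned mediation partly addresses the middle link. It cannot test whether participation or social involvement opportunities (and enjoyment, on the broader reading) explain the arms' psychosocial differences. Of three links, one is partly covered and two are not covered at all.

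The size is qualitative; no error rate or sample size figure is involved, and the primary comparison of arms is unaffected. The conclusion assumes that the Analysis strategy section gives the full purpose and dependent variable of the objective 2 analysis. The change is worth making before analysis, which the Trial status section expects to continue through 2022.

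**What to change.** Choose one of two routes.

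**Route 1: add the missing models.**
- Keep the cross-arm motives-to-participation model, and state condition as the predictor in it, so that the condition → motives → participation link is estimated. Moving it under secondary objective 1 would lose the comparison across arms.
- Add mediation models with randomized condition as predictor (team versus individual, and each sport versus control). The mediators are participation, enjoyment and social involvement opportunities. The dependent variable is the SF-12 at 3 months, adjusted for its baseline value.
- Adjust mediators for baseline where one was measured. Participation has none, so use the 6-week and 3-month attendance reports and say what participation means in the control arm. The 3-month report is collected at the same visit as the outcome; the 6-week report precedes it.
- Report each indirect effect with an interval.
- Do not use enjoyment as both mediator and outcome in the same model. The aims list it among the psychosocial outcomes, while the mediation hypothesis uses it as an explanation.
- Describe the mediator-to-outcome path as observational, because only condition is randomized.

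**Route 2: narrow the hypothesis.** Restrict secondary question 2 to motives and participation, and draw no mediation conclusion about psychosocial outcomes.

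Route 1 costs analysis wording and extra programming, with no new data collection; its lasting weakness is the observational second path. Route 2 costs almost nothing but gives up the mechanistic claim about psychosocial benefit.
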